## Sample size

The small sample size in this study reflects the rarity of the patient cohort, influenced by factors such as the low prevalence of the tumour type, delays in presentation and diagnosis, and post-treatment survival rates.

Recruitment and sample size will be guided by the principle of data saturation [44]. Hennink and Kaiser [45] suggest that qualitative data saturation is achieved with 9–17 participants for semi-structured interviews and 4–8 participants for focus groups.

**Phase 1a: Online Survey**– Up to 45 participants.**Phase 1b: Semi-structured Online Interviews**– Up to 10 participants.**Phase 2: Co-design Users**– Up to 6 participants.**Phase 3: Test Users**– Up to 6 participants.

To determine the sample size for Phase 1a, a calculation [46] was conducted using a 95% confidence level, a 5% margin of error, and an estimated population proportion of 3% within a population of 67 million. Based on these parameters, a sample size of 45 participants was deemed sufficient.

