### Phase 3: test

Phase 3 of the PiCTuRE study will evaluate the newly co-designed, interactive, personalised digital consent platform, aiming to promote patient autonomy, shared decision-making, and personalised consent. Outcomes will be measured through both qualitative and quantitative methods, with a focus on user experience. Post-intervention, a survey and semi-structured interviews will be conducted to assess participant feedback and explore their lived experiences, including their views on discussing tissue donation for research with healthcare professionals. This phase will provide insights into the effectiveness of the intervention, with Patient Reported Experience Measures (PREMs) used to gather data on satisfaction and engagement [39, 40]. The qualitative data will help validate the quantitative findings and assess the overall success of the intervention [41]. Additionally, user feedback from post-intervention interviews will be analysed for statistical significance, contributing to the refinement of the intervention, and providing evidence for a potential new standard of care in cancer patient consent processes.

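### Phase 3 interviews are capped at 6 people, below the 9–17 saturation range that the protocol cites for semi-structured interviews

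*Protocol article*

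**What the plan says.** The Sample size section of the protocol article opens by explaining the small numbers by the rarity of the cohort. It then gives a general principle: "Recruitment and sample size will be guided by the principle of data saturation". It supports this with a cited source, according to which "qualitative data saturation is achieved with 9–17 participants for semi-structured interviews and 4–8 participants for focus groups".

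The caps for all phases follow directly. For the phases considered here they are:

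- Phase 1b, semi-structured online interviews: "Up to 10 participants".
- "Phase 2: Co-design Users– Up to 6 participants".
- "Phase 3: Test Users– Up to 6 participants".

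Only Phase 1a, the online survey, has a separate calculation for its size.

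The section Phase 3: test describes the method for the test users: "Post-intervention, a survey and semi-structured interviews will be conducted to assess participant feedback and explore their lived experiences". The Phase 3 part of Data analysis again names online semi-structured interviews as the source of the qualitative data after the intervention.

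**The concern.** A reader who takes the Sample size section at its word will apply the interview range to every phase that uses semi-structured interviews. Phase 3 is such a phase, and its maximum is below the bottom of that range. The principle, the range and the cap stand within a few lines of each other and do not fit together.

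This bears on what Phase 3 may be said to show. According to the section Phase 3: test, its qualitative data help to judge whether the platform has succeeded, and its findings contribute evidence towards a possible new standard for consent in cancer care. If the interviews appear to rest on a saturation argument, readers may treat the range of views collected as complete. On the protocol's own figures, the design gives no ground for that.

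**Working it through.** **The one size that the protocol calculates.** Phase 1a uses 95% confidence, a 5% margin of error, a proportion of 3% and a population of 67 million (Sample size).

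- Formula: n = z² × p(1 − p) / d², with z = 1.96 (97.5th normal percentile), p = 0.03, d = 0.05.
- Result: n = 44.71 (z unrounded), rounded up to 45. The finite population correction leaves it at 45.

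This reproduces the stated 45. It has no bearing on the interview phases, whose caps come with no calculation. For those the check is a direct comparison of cap and cited range.

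**Comparison by phase** (all figures from Sample size; methods from the phase descriptions and Data analysis)

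| Phase | Method | Cap | Cited range | Cap inside range? |
|---|---|---|---|---|
| 1b | Semi-structured interviews | 10 | 9–17 | Yes: 10 − 9 = 1 above the lower end |
| 2 | Co-design group sessions | 6 | 4–8 (focus groups) | Yes |
| 3 | Survey and semi-structured interviews | 6 | 9–17 | No: 9 − 6 = 3 below the lower end, 17 − 6 = 11 below the upper |

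**Does the interview range apply to Phase 3?** Three steps lead to yes.

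1. The saturation sentence is not limited to one phase, and it precedes the list of all phases.
2. The method in Phase 3 is named as semi-structured interviews in two separate places, so the focus-group range is not the relevant one.
3. Interviewees in Phase 3 are drawn from its test users, so there cannot be more than 6 of them.

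Because 6 is a maximum, no recruitment outcome closes the gap of 3. Lower recruitment widens it.

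**The case against.** The strongest defence is that the protocol openly gives another reason for small numbers, the rarity of the cohort, and that saturation only guides the size. The source is cited as suggesting its ranges, and nowhere does the protocol promise that Phase 3 will be saturated. The participants are called test users, the phase focuses on user experience, and its results also rest on a survey and on patient-reported experience measures. All of this stands. It shows that a cap of 6 may be reasonable, but it does not make 6 consistent with 9–17. It points to the proper justification, which the text should then give for Phase 3.

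A second defence is that saturation was meant for Phase 1b alone. The wording does not say so, and one sentence would settle it.

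Two stronger readings are tempting, and the document does not support them.

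- A reader might infer that Phase 1b also misses the range, because 10 is a ceiling close to the lower end and no minimum or stopping rule is given. But 10 lies within 9–17, the upper end is not a requirement, and a maximum is compatible with stopping once saturation appears. A minimum and a stopping rule are operational detail that a condensed article may leave to the full protocol.
- A reader might infer that less common barriers to donation will be missed, and try to express this as the chance that a barrier is mentioned at least once in a given number of interviews. The platform is also informed by open-ended answers from up to 45 survey respondents, and Phase 1 is underpinned by a scoping review. Such a calculation would leave both out. It would also measure first mention rather than saturation, and it would apply a question about barriers, mainly the task of Phase 1, to a phase that tests a finished platform.

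**Conclusion.** The point holds for Phase 3 only. The saturation basis stated in Sample size cannot be met there: the cap of 6 is 3 below the cited lower end even with full recruitment. Neither the rarity of the cohort nor the focus-group range reconciles the two. Phases 1b and 2 are consistent with the ranges cited for them.

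The conclusion rests on two readings of the text: that the saturation principle covers all phases listed after it, and that the cap of 6 is the total number of people available for interview in Phase 3. It does not depend on whether 9–17 is the right range, since the comparison uses the protocol's own figures.

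The fault lies in the justification and in what may be claimed from it. It does not show that 6 test users are too few for user testing.

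**What to change.** In Sample size, keep the Phase 3 cap and change its basis:

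- State that the Phase 3 number rests on feasibility, given the rarity of the cohort, and that it is a user-testing sample.
- Limit the saturation principle and the 9–17 range to the phase they fit, Phase 1b, so that they no longer appear to justify Phase 3.
- Make no saturation claim for the Phase 3 interviews.

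In Phase 3: test, and in the Phase 3 part of Data analysis where effectiveness is assessed, limit the conclusions accordingly. The interviews can describe how these users experienced the platform. Statements about its overall success, or about a new standard for consent, should be worded as preliminary.

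No participants, data collection or analyses are added. The cost is a less favourable claim for Phase 3.

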## Introduction

Primary brain and spinal tumours are individually rare, accounting for less than 3% and 1% of all cancer diagnoses in the UK, respectively [1, 2]. Rare cancers, by definition, have an incidence of fewer than 6 cases per 100,000 people [3]. Glioblastoma, the most common primary brain tumour in the UK, affects 3–4 people per 100,000 [1]. Primary spinal tumours, including those of bone and soft tissue (sarcomas), are even rarer, with fewer than 120 cases diagnosed annually in the UK [ [2, 4].

Together, these tumours impose a significant burden on patients, their families, and society. Diagnoses are often delayed, and there are limited integrated translational research programmes (spanning from biology to clinical trials) dedicated to addressing these conditions.

Patients are entitled to a timely and accurate diagnosis, which serves as the foundation for the implementation of novel “personalised” or “precision” medicine approaches, typically defined in biological terms. Equally important, however, is the consideration of patients’ perspectives and experiences when undergoing “personalised” treatment for these tumours. It is essential to understand their priorities, address their concerns, and ensure that treatment strategies align with their values and preferences [5–9].

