## Participant sampling and selection

The PiCTuRE study will be promoted across various digital platforms, including social media, charity websites, and patient support sites, using posters and e-flyers. Given the rarity of the target population, a multistage purposeful random sampling method [42] will be employed to encourage enrolment and identify individuals interested in participating in online semi-structured interviews, collaborating on the co-design of the digital platform, and providing feedback during the testing phase. Recognising the lack of inclusivity in research involving diverse populations, recruitment may also be supplemented through snowball sampling [43] via social media networks and outreach to ethnic community groups. Participants will receive the study information upon clicking the link provided in the online advertisements. An overview of the inclusion and exclusion criteria for all three phases of the study is outlined in Table 1.

**Table 1 Tab1:** Overview of inclusion and exclusion criteria for phases 1 to 3

Inclusion Criteria	Exclusion Criteria
Proficiency in speaking and understanding English	Inability to communicate effectively in English
Aged 18 years or older	Under the age of 18 years old
Lived experience of having a primary tumour of the brain or spine	Unable to provide informed consent
Capable of providing informed consent	No access to internet-enabled devices (e.g., smartphone, tablet, computer)
Able to communicate via digital media	Unable to communicate using digital media
Access to an internet-enabled device (e.g., smartphone, tablet, computer)	

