## Data analysis

### Phase 1a

The findings from the online cross-sectional survey will be reported in alignment with the Consensus-Based Checklist for Reporting of Survey Studies (CROSS) [44]. Thematic analysis [31] be employed to examine open-ended responses, identifying key themes and patterns. Recurring codes and themes will be subjected to comparative analysis across demographic and clinical segments, such as age groups, gender, and diagnosis. Descriptive statistics will be utilised to contextualise the themes generated through qualitative analysis. Additionally, correlation analysis will be conducted to explore relationships between variables.

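### The Phase 1a survey size of 45 comes from a ±5-point precision calculation at an assumed 3%, a value that fits no survey question; at 45 respondents the margin is about ±9 to ±15 points for answers between 10% and 90%

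*Protocol article*

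**What the plan says.** The Sample size section of the protocol article sets the Phase 1a online survey at "Up to 45 participants". It first attributes the small sample to the rarity of the cohort and says that data saturation will guide recruitment. It then gives a separate calculation for Phase 1a, "using a 95% confidence level, a 5% margin of error, and an estimated population proportion of 3% within a population of 67 million", and concludes: "Based on these parameters, a sample size of 45 participants was deemed sufficient". It does not say what the 3% measures.

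Three other places bear on this:

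- **Introduction.** Primary brain and spinal tumours are described as "accounting for less than 3% and 1% of all cancer diagnoses in the UK, respectively". This is the only other 3% in the article.
- **Participant sampling and selection, Table 1.** Inclusion requires "Lived experience of having a primary tumour of the brain or spine".
- **Data analysis, Phase 1a.** Thematic analysis of open-ended answers comes first. In addition, "Descriptive statistics will be utilised to contextualise the themes generated through qualitative analysis", themes are compared across demographic and clinical segments, and correlations are explored.

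**The concern.** In a precision calculation for one proportion, p is the share of the surveyed population expected to give a particular answer. Here it is 3% of 67 million UK residents. The survey does not sample UK residents at large. It samples people who have had one of these tumours, so the tumour proportion among respondents is 100% by design. If p is meant as tumour frequency, the survey cannot estimate it. If p is meant as a survey answer, the article names no question with an expected answer near 3%.

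The choice matters because p(1 − p) is small at 3% and largest at 50%. A very low p is what lets a ±5-point margin be met with so few people. At stake is the only sample-size calculation in the article: it implies a precision for the descriptive survey results that 45 respondents cannot give across almost the whole range of possible answers.

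**Working it through.** **Inputs (Sample size section).** Confidence 95%, so z = 1.96; margin e = 0.05; p = 0.03; N = 67,000,000.

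**1. Reproduce the stated figure.** n₀ = z²·p(1 − p)/e² = 1.96² × 0.03 × 0.97 / 0.05² = 44.7. The finite-population correction, n₀/(1 + (n₀ − 1)/N), leaves it at 44.7 because N is so large. Rounded up, n = 45, which agrees with the article.

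**2. Where ±5 points holds at n = 45.** Solve 1.96·√(p(1 − p)/45) ≤ 0.05. This requires p(1 − p) ≤ 0.05² × 45 / 1.96² = 0.0293, so p ≤ about 3.0% or p ≥ about 97.0%. At p = 3% the half-width is ±4.98 points, so there is no slack. With 44 respondents it is already ±5.04.

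**3. Precision at other proportions.** Half-width = 1.96·√(p(1 − p)/45); required n = 1.96²·p(1 − p)/0.05², rounded up.

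| True proportion | 95% half-width at n = 45 | n needed for ±5 points |
|---|---|---|
| 3% (or 97%) | ±5.0 points | 45 |
| 10% (or 90%) | ±8.8 points | 139 |
| 20% (or 80%) | ±11.7 points | 246 |
| 30% (or 70%) | ±13.4 points | 323 |
| 50% | ±14.6 points | 385 |

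As a check without the normal approximation, 23 of 45 (51.1%) has a Wilson interval of 37.0% to 65.0% and a Clopper-Pearson interval of 35.8% to 66.3%.

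**4. Does the population size rescue it?** The article does not give the number of eligible patients. Assuming anything from 500 to 100,000 in place of 67 million, the worst-case half-width at n = 45 is ±13.9 to ±14.6 points, and ±5 points needs 218 to 383 respondents. The result is not sensitive to N.

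**5. Do the two inputs belong together?** Read literally, 3% of 67 million is 0.03 × 67,000,000 = 2.01 million people, in a cohort that the same section calls rare. If the 3% was taken from the Introduction, its denominator is cancer diagnoses, not residents.

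**6. Sampling.** The formula assumes a simple random sample. The article describes an anonymous survey advertised on social media, charity and patient-support sites, with possible snowballing. It calls its method purposeful random sampling, but that label does not make volunteers answering an open link a probability sample. The margins above are therefore optimistic.

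**The case against.** The best defence is that Phase 1a is mainly qualitative. Its primary analysis is thematic, descriptive statistics give context, and correlations are exploratory. No survey proportion is a named endpoint, and no hypothesis or progression decision depends on ±5 points. The section also cites rarity and saturation, and a ceiling of 45 is compatible with stopping once saturation is reached. All of this stands, and it limits the seriousness of the point. It does not rescue the calculation. The saturation benchmarks quoted (9–17 and 4–8) are for interviews and focus groups, the calculation is what the section gives as determining the Phase 1a size, and quantitative summaries of the survey are planned.

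Several stronger readings are tempting but unsupported:

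- *The 3% is the share of cancer diagnoses.* This is likely, but inferred; the Sample size section names no source for it. The conclusion does not need it.
- *The eligible population can be counted from the 6 per 100,000 in the Introduction.* "Rare cancers, by definition, have an incidence of fewer than 6 cases per 100,000 people" defines a rare cancer. It is not given as the incidence of all eligible tumours, and an annual incidence would not match eligibility by lived experience.
- *Survey results are three times less precise than stated.* That is the worst case: 14.6/5 = 2.9 at 50%, but 8.8/5 = 1.8 at 10%.
- *Results will be reported as accurate to ±5 points.* The article uses ±5% as an input and nowhere says that results will carry that margin.
- *Forty-five is the wrong number.* It may well be defensible on feasibility. Only its stated justification fails.

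**Conclusion.** The concern holds as a mismatch between the calculation and its purpose, not as an arithmetic error. The stated inputs give 45, but they describe a 3% characteristic of the general population, while the survey describes answers from people who all have the condition. At 45 respondents the claimed ±5 points applies only at or beyond about 3% and 97%; between 10% and 90% the half-width runs from ±8.8 to ±14.6 points.

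These figures rest on the normal approximation, full recruitment to 45, complete answers to each question and simple random sampling. Fewer answers would widen them, and the last assumption is not met. Because the phase is mainly qualitative and nothing formal depends on the margin, this is a correction that should be made rather than one on which the study turns.

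**What to change.** In the Sample size section, delete the calculation based on 95%, 5%, 3% and 67 million. Keep up to 45 as a pragmatic maximum, justified by rarity, feasibility and saturation of the open-ended responses, and state the precision it gives. For example:

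*Up to 45 survey participants is a pragmatic maximum reflecting the rarity of these tumours, feasibility of recruitment and expected saturation of open-ended responses. With 45 respondents, an observed proportion of 50% would have a 95% margin of about ±15 points, and one of 10% about ±9 points. These margins presume random sampling; survey percentages describe respondents only.*

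The cost is a change of wording and a less favourable stated precision. No extra participants are needed, and the design and analyses stay as they are.

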## Data storage

All electronic data will be password-protected and stored on secure university servers, while paper documentation will be kept in a locked research facility accessible only to authorised researchers. Survey data will be transferred to password-protected Excel files. Audio recordings will be deleted from devices after being securely shared with an approved transcription service. Final transcriptions will be stored as password-protected Word documents on encrypted university servers, with original audio files permanently deleted.

## Data analysis

### Phase 1a

The findings from the online cross-sectional survey will be reported in alignment with the Consensus-Based Checklist for Reporting of Survey Studies (CROSS) [44]. Thematic analysis [31] be employed to examine open-ended responses, identifying key themes and patterns. Recurring codes and themes will be subjected to comparative analysis across demographic and clinical segments, such as age groups, gender, and diagnosis. Descriptive statistics will be utilised to contextualise the themes generated through qualitative analysis. Additionally, correlation analysis will be conducted to explore relationships between variables.

### Phase 1b

Audio recordings from online interviews will be transcribed verbatim using professional transcription services to ensure accuracy and consistency. The transcriptions will then be processed in qualitative analysis software (NVivo) for detailed examination and coding. Thematic analysis [32] will be employed as the primary methodology, relying on a thorough textual analysis of the transcribed content to generate a precise and reliable dataset for subsequent analysis.

### Phase 2

PREMs outcome data will be analysed using a Statistical Package for the Social Sciences (SPSS). Correlation analysis will identify relationships between variables using correlation coefficients. Regression models will evaluate the impact of multiple variables on specific outcomes, while an Analysis of Variance (ANOVA) will assess statistically significant differences between groups. Quantitative data will be supplemented by content analysis [2, 30] of audio collected via the online co-design group sessions.

Sequential data analysis will examine the connections between findings from Phase 1 and Phase 2. These results will be triangulated to guide and inform the implementation of Phase 3.

### Phase 3

Post-intervention user experience data collected via PREMs will be analysed using the methodology outlined in phase 2 and statistically compared to the corresponding phase 2 data. Quantitative findings will be enriched by qualitative insights obtained from post-intervention online semi-structured interviews. The integration of mixed-methods data [38, 44] will facilitate a comprehensive assessment of the effectiveness of the newly developed digital tool.

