**Methods & Analysis:**

PiCTuRE is a multistage, mixed-methods, exploratory sequential investigation aimed at understanding the lived experiences of individuals donating tissue for research. It consists of three phases: Phase 1 involves an online survey to collect lived experience data, followed by semi-structured interviews to further explore individual perspectives. Thematic analysis will be performed to identify key themes. In Phase 2, patient-reported experience data will be gathered through co-design and statistically analysed to validate content for the development of the digital platform. Phase 3 will refine this intervention through iterative cycles of Phases 1 and 2, in collaboration with patients with lived experience of brain or spine tumours, to prepare it for integration into routine clinical practice.

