### Phase 2: build

Phase 2 of the PiCTuRE study focuses on the development of the digital intervention through co-design methods. Patient-reported experience data will be collected and statistically analysed to validate and refine the digital consent tool [33] Co-design and experience-based co-design approaches have proven effective in enriching the development of patient-facing interventions [34–36]. To gather feedback, two Patient Reported Experience Measures (PREMs) will be used: (1) the Client Satisfaction Questionnaire (CSQ-8), an 8-item measure to assess satisfaction with the digital platform [17, 37], and (2) a 5-item Shared Decision-Making (SDM) tool, CollaboRATE [38], which asks participants to rate the quality of their provider’s communication regarding decision making.

These tools will help capture patient perspectives on the digital intervention. Data from Phase 1a and 1b, including qualitative findings, will be integrated to further personalise and refine the digital consent tool. Participants from Phase 1b will be invited to review the online tool and provide feedback, which will be used to improve the platform. The collected satisfaction and experience data will be analysed to validate items for subsequent use, guiding the next steps in the tool’s development and ensuring that it effectively meets patient needs.

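### Phase 2 plans correlation, regression and ANOVA to validate items and content on data from at most 6 co-design users, a number that cannot support those methods

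*Protocol article*

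**What the plan says.** The Sample size section sets Phase 2 (co-design users) at "Up to 6 participants", and gives Phase 3 (test users) the same ceiling. It guides recruitment by data saturation. Its only calculation is for the Phase 1a survey.

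The Phase 2 description names two instruments: "the Client Satisfaction Questionnaire (CSQ-8), an 8-item measure to assess satisfaction with the digital platform", and "a 5-item Shared Decision-Making (SDM) tool, CollaboRATE". Of the resulting data it says: "The collected satisfaction and experience data will be analysed to validate items for subsequent use". The Abstract (Methods & Analysis) says that the co-design data will be "statistically analysed to validate content for the development of the digital platform".

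The Data analysis section, under Phase 2, names three methods for the PREM data. The first is correlation: "Correlation analysis will identify relationships between variables using correlation coefficients". The other two follow: "Regression models will evaluate the impact of multiple variables on specific outcomes, while an Analysis of Variance (ANOVA) will assess statistically significant differences", the differences being between groups that are not named. Content analysis of the co-design audio is given a supplementary role. Under Phase 3, the same section applies the Phase 2 methods again and adds a statistical comparison of the two phases.

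**The concern.** The protocol fixes both the methods and the number of people, and the two do not fit. Multi-variable regression and ANOVA need residual degrees of freedom to estimate error, and six observations leave almost none. At this size only a very large estimate can be significant, so whatever is reported as significant will usually overstate the true relationship.

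The stated purpose makes this matter. A reader of the Phase 2 report would take a statistically validated item or content element as established, and it would enter Phase 3 with that label. Phase 3 then repeats the methods on at most 6 users. A later analysis plan could name the variables and groups, but it could not make these tests informative at the stated size.

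**Working it through.** **Inputs.** Phase 2 n ≤ 6 and Phase 3 n ≤ 6 (Sample size). Phase 1b n ≤ 10, used as a sensitivity case because the Phase 2 description invites Phase 1b participants to review the tool. No significance level is given for Phase 2, so two-sided 5% is assumed. The numbers of predictors and groups are not stated; the values below are illustrations. Because 6 is a ceiling, the n = 6 results are the most favourable for that cap.

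**The plan's own figure.** Phase 1a: n = z²p(1-p)/d² = 1.96² × 0.03 × 0.97 / 0.05² = 44.7, rounded up to 45. This reproduces the stated 45. It concerns the survey only; the Phase 2 cap has no power or precision statement to check.

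**Correlation, n = 6.**
- Critical value: r = t/√(n-2+t²), with t = 2.776 on 4 df, gives 2.776/√(4 + 7.706) = 0.811.
- Interval for an observed r = 0.5 (Fisher z): 0.549 ± 1.96/√3 = 0.549 ± 1.132, which transforms back to -0.52 to 0.93.
- Power (simulation, 200,000 bivariate normal samples): 9%, 17% and 37% for true r = 0.3, 0.5 and 0.7.
- Exaggeration: when the true r is 0.5, the significant estimates average |r| of about 0.88.

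**Regression, n = 6.** With k predictors, residual df = 6-k-1. The expected R² with no association is k/(n-1) = k/5. The R² needed for significance is kF/(kF+df), where F is the 5% critical value on k and df degrees of freedom.

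| k | Residual df | Expected R² by chance | R² needed |
|---|---|---|---|
| 2 | 3 | 0.40 | 0.864 |
| 3 | 2 | 0.60 | 0.966 |
| 4 | 1 | 0.80 | 0.999 |
| 5 | 0 | 1.00 | no test possible |

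At a true R² of 0.5, power is 25%, 14% and 8% with 2, 3 and 4 predictors.

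**ANOVA, n = 6 (assumed splits).** Two groups of 3: power is 12% for a difference of 0.8 SD, and 80% power needs about 3.1 SD. Three groups of 2: power is 8% at f = 0.4.

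**Sensitivity, n = 10.** With t = 2.306 on 8 df, critical r = 2.306/√(8 + 5.318) = 0.63. Power for a true r of 0.5 is about 33% (simulation). The interval for an observed 0.5 is 0.549 ± 1.96/√7, or -0.19 to 0.86.

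**Phase 3 against Phase 2, 6 vs 6.** Treated as independent groups (the protocol does not say whether users overlap), 80% power needs a difference of about 1.8 SD.

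**The case against.** The best defence is that this is an exploratory sequential mixed-methods study with a strong qualitative strand. The tool is refined through participant feedback, Phase 1 findings, content analysis and triangulation, and the thematic analysis in Phase 1 is also said to validate items. On that view the statistics are secondary. Part of this stands: the harm from the tests is diluted by the other evidence. But the exploratory label describes the overall design. The Phase 2 analysis is itself worded as significance testing and validation, and the label adds no degrees of freedom. Nor does the possibility that all Phase 1b participants supply PREM data rescue it, as the n = 10 results show.

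Several stronger readings are tempting, and the document does not support them:

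- *That any significant result is mostly noise.* One pre-specified test keeps a 5% false-positive rate if its assumptions hold. The false share among significant results is 0.05(1-π)/[0.05(1-π) + power × π], where π is the proportion of real effects. Over powers of about 9% to 37% it is 55-84% for π = 0.10, 29-64% for π = 0.25 and 12-37% for π = 0.50. The document gives no basis for choosing π.
- *That the regressions are saturated.* This needs 5 predictors, and the protocol gives no number.
- *That there are no groups to compare.* Phase 2 has no comparator arm, but participant subgroups could serve; the Phase 1a analysis names age group, gender and diagnosis. The groups are undefined, which an article may leave to a fuller document.
- *That 13 items yield 78 correlations and about 3.9 false positives (78 × 0.05).* This assumes item-level testing, which is not stated, and no true correlations, which is unlikely for items of one scale. For the same reason |r| above 0.81 is not implausible in itself.
- *That content will be kept or dropped on p-values.* No section says so.

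**Conclusion.** The point holds in this form: the inferential methods named for Phase 2 are not supportable at n ≤ 6, and the claim that they validate items or content is unsupported. The central figures are a significance threshold of |r| = 0.81, about 17% power at a true r of 0.5, and an interval from -0.52 to 0.93 around an observed 0.5. These rest on an assumed two-sided 5% level and, for correlation, bivariate normality. The regression and ANOVA figures also rest on assumed numbers of predictors and groups, but the conclusion does not depend on which are chosen: with as few as 2 predictors, R² must exceed 0.86. The defects shown are low power, very wide intervals and exaggerated significant estimates. A particular false-positive share is not shown. The same weakness carries into Phase 3 through the reuse of the methods and the comparison between phases.

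**What to change.** - **Data analysis, Phase 2:** replace the correlation, regression and ANOVA tests with descriptive reporting: each participant's CSQ-8 and CollaboRATE scores, median and range, and response counts per item. Any coefficient shown should be labelled descriptive and carry no p-value.
- **Same section:** make the content analysis of the co-design sessions the main basis for refining the tool, with the scores in support.
- **Abstract (Methods & Analysis) and Phase 2 description:** remove the claim that statistical analysis validates content, items or the tool; say that the data inform refinement.
- **Data analysis, Phase 3:** make the same change to the sentence that reuses the Phase 2 methods and compares the phases statistically, so that it does not refer to methods that have been removed. Present the two phases side by side descriptively. The statement in the Phase 3 description that interview feedback will be analysed for statistical significance should be brought into line.

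The cost is a wording change and less analysis work, with no effect on recruitment. The downside is that the Phase 2 and Phase 3 reports will contain no p-values.
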